**3. Study Design and Clinical Setting**

The study will be conducted over 6 months from May 2016 to October 2016 in three big cities in Jordan (Amman, Mafraq, Zarqa); on Syrian refugees that reside in these two areas. The study will follow the single-blinded randomized controlled trial. Eligible patients will be randomized into two groups, intervention and control. Predetermined randomization number list which will be designed through computer-generated randomization program will be available before starting the study. The patients will be invited to participate in the study and he/she will be asked to sign the informed consent form. Only Syrian refugees who meet all of the following inclusion criteria will be recruited into the study: (1) Living in Jordan for more than six months and intending to stay for the study period which is six months. (2) Being above the age of 18 years. (3) Having at least one chronic condition or taking 5 or more medications or taking more than 12 doses of medication per day. The Exclusion criteria for this study will include: (1) Patients with cognitive or sensory impairment that may prevent conducting the interview. (2) Patients who are planning to travel within the next six months after the baseline home-visit. (3) Patients who are not capable of reading or writing Arabic.

**4. Study Protocol:** Figure (1) shows the concert for the study protocol

Patients Eligibility: patients that meet the recruitment criteria will be invited to participate in the study

The patients will be interviewed at their homes to collect all needed information. The patients will be asked to answer the self-completion questionnaires (Quality of life, scale of anxiety, knowledge of medication, adherence)

Pharmacist counseling will be conducted for intervention group only

The pharmacist will interview the patients 2-3 months post baseline

The patients in intervention group will be asked to visit the physician to confirm these changes

The approved recommendations for control group patients will be kept until the end of the study

The physician will approve part of the recommendations

A report will be written for the physician

The pharmacist will conduct the medication review for all patients

Control group

Intervention group

Randomization

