Eligible patients who will fulfill the including criteria will be randomized into two groups, intervention and control groups. Patients will be informed on the nature of the study and will be asked to sign informed consent form. Patients in both intervention and control groups will be interviewed at their homes to assess their use of the treatment and to collect all relevant information. In addition, they will be asked to answer the quality of life questionnaire, the self-reported adherence questionnaire, knowledge about medication questionnaire and the scale of anxiety questionnaire. Medication review (explained in the next section [5]) will be conducted for both intervention and control groups. Only patients in intervention group will receive counseling that does not exceed the clinical pharmacist role (explained in the next section [6]). This will be followed by writing a report to the physician with the findings and recommendations. The report will be delivered to the physician directly with references supported by current guidelines. The physician will tick the recommendations approved and return to the researcher, allowing the clinical pharmacist to convey the approved changes to the patient. The patients will be asked to visit their physician for confirmation of changes. Patients in the active and the control group will be interviewed 2-3 months post baseline, assessing changes in treatment, number of treatment related problems, changes in the quality of life, changes in self-reported adherence, changes in anxiety level and changes in patients’ knowledge about their medication. Patients in the intervention group will provide their perspective of MMR service (role of the pharmacist, value of the service they received, and willingness to pay for such services).

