As for the control group, home interview will also be conducted, but no intervention (patient counseling or returning the physician's report) will be done until the end of the study. Questions from control group patients will be recorded and answered at the end of the study. The recommendations that approved by the physician concerning the control group will be returned back to them directly after the study period finished. The pharmacist will ask the patients in the control group to visit the physician to confirm these changes. Patients in control group with life-threatening TRPs will be excluded from the study (serious drug-drug interactions, medication high dose that may damage kidney or liver function over time, serious drug-disease interaction, pregnancy-related problems (including mother and fetus), occurrence of sudden health episode or complication during the study period (Carolan *et al*., 2016)).

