**5. Medication Review:**

The Australian model for medication review service will be followed in this study (since this service does not exist yet in the country). The clinical pharmacist will interview the patients at their own homes; collect all the information relevant to their medications and health conditions including current diseases, current drugs, history of previous diseases and drugs, side effects and allergy. This will be followed by interpretation and analyzing of the information regarding the patient’s medical history, current therapeutic regimen along with any needs and concerns; identifying therapeutic and other issues relevant to the short and long term management of the patient; making appropriate recommendations regarding the clinical information gathered for consideration by a physician.

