**8. Follow-up Assessments**

Both groups will be revisited at their homes 2-3 months after the baseline assessment. This assessment traces changes in treatment, number and type of TRPs, adherence, anxiety, quality of life and patients’ knowledge about medication (Figure 1). A collective report highlighting the feasibility and success of the study will be submit to the involved physicians three months following the end of the study.

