**15. physicians’ approval rate of the Pharmacist Recommendations**

After the medication review, all the pharmacist’s recommendations will be sent to the physicians to take the approval from them. The physicians will approve some of these recommendations. To calculate the approval rate for the pharmacist recommendation, the total number of approved recommendations by physicians will be divided by the total number of all recommendations (approved + rejected) sent to the physicians.

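### A control with a life-threatening treatment-related problem is excluded after randomisation, with no written duty to warn the patient or alert the physician when it is found

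*Protocol*

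**What the plan says.** In section 4 (Study Protocol), eligible patients are randomised, both groups are interviewed at home, and both receive the pharmacist's medication review. For controls, "no intervention (patient counseling or returning the physician's report) will be done until the end of the study". Their questions are noted and answered only when the study is over. On physician-approved changes, the section says "The recommendations that approved by the physician concerning the control group will be returned back to them directly after the study period finished", and only then are controls asked to see the physician. The Figure 1 text agrees: "The approved recommendations for control group patients will be kept until the end of the study".

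The paragraph on controls then turns to serious findings: "Patients in control group with life-threatening TRPs will be excluded from the study". It lists what qualifies: serious drug-drug interactions, high doses that could harm kidney or liver over time, serious drug-disease interactions, pregnancy-related problems, and a sudden health episode or complication during the study. No other action is attached to the list.

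The physician has a routine channel. Section 4 says "The report will be delivered to the physician directly with references supported by current guidelines". Section 5 (Medication Review) describes the output as "making appropriate recommendations regarding the clinical information gathered for consideration by a physician". Section 15 says that all the pharmacist's "recommendations will be sent to the physicians to take the approval from them". Section 8 (Follow-up Assessments) says "Both groups will be revisited at their homes 2-3 months after the baseline assessment". Section 16 (Sample size) names TRP improvement before and after the service as the primary outcome variable.

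**The concern.** The trial looks for TRPs in controls and, by design, holds back what it finds. Such a design needs a clear rule for findings too dangerous to hold. The protocol recognises this class of patient, but its written response is only to take the patient out of the study. Two things are at stake.

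- **Safety.** If nothing says who is told and when, the warning depends on what the pharmacist decides to do. A control could keep taking an interacting drug or an excessive dose while a routine approval form is pending.
- **Validity.** Patients are dropped after allocation, in one arm only, for a reason tied to the primary outcome. The groups compared at follow-up are then no longer the groups that were randomised.

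**Working it through.** No arithmetic applies. The check sets the relevant provisions side by side.

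1. **When the problem is found.** Section 4 places randomisation before the interview and the medication review, and the rule is written for patients already in the control group. The last listed trigger can arise only during the study. The exclusion is therefore post-randomisation.

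2. **What must happen at detection.** The control-group paragraph requires exclusion. Section 4 otherwise, the Figure 1 text, and sections 5, 6, 7, 8, 14 and 15 add no step specific to a life-threatening TRP: no notice to the patient, no expedited notice to the physician, no check that the problem was resolved.

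3. **Whether the routine report fills the gap.** It partly does. A report is written after every patient is reviewed, and section 15 exempts neither arm. The reference in section 4 to physician-approved recommendations for controls presupposes that their reports are sent. But the protocol gives no time by which the report must go, does not ask for dangerous items to be marked, and does not say whether the report still goes out once a control is excluded.

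4. **Whether the report reaches the patient.** In section 4 the physician ticks approvals and returns them to the researcher. For intervention patients the pharmacist then passes the changes on. For controls the approved changes are held to the end, and questions go unanswered until then. None of these provisions carries a written exception for danger.

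5. **Which arm loses patients.** The exclusion rule names the control group only. An intervention patient with the same interaction or overdose stays in, is counselled and is assessed at follow-up. The two arms are treated differently on a characteristic that bears directly on the TRP outcome.

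6. **Direction of the resulting bias.** It is not fixed by the text. Dropping controls who suffer a complication during the study removes poor control outcomes and makes the control arm look better. Dropping controls with serious TRPs at the baseline review makes the arms unlike at the start, and the effect on the change score depends on how many TRPs those patients had and how these would have evolved. The protocol gives neither.

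7. **Follow-up.** The home visit at 2-3 months is the only later study assessment. The protocol does not say whether an excluded control keeps it.

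**The case against.** The strongest reply is that exclusion is itself the safety exception. The holds apply to controls in the study, the exclusion sentence follows them in the same paragraph, and a patient who is out of the study is no longer held. That is a plausible reading of the intent, and I accept it. A reader might go further than this point does and infer that the protocol forbids warning a control in danger; the text does not support that. But release from a hold is not an instruction to warn.

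Second, the physician is not left uninformed. A reader might infer that no physician hears of the problem, but the routine report goes to physicians for both arms. What is open is its speed, its flagging, and whether it is sent after exclusion.

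Third, a reader might infer that excluded controls lose the 2-3 month visit. That is the usual consequence of exclusion, but the protocol does not say so.

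Fourth, the triggers are not alike. A patient normally knows of a sudden health episode, so a duty to tell the patient adds little there, and a dose that may do harm over time is less urgent than a dangerous interaction. This stands and is reflected in the fix.

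Fifth, the consent pages are not in this copy, and section 2 requires ethics approval. Either might provide for disclosure, and this cannot be checked. It would answer the safety part but not the one-arm exclusion.

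Finally, one sentence on notification would close the safety gap without abolishing exclusion. That is true of the safety gap alone. Keeping the patient is justified separately, because the exclusion breaks the randomised comparison.

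**Conclusion.** The point holds in this form: exclusion is the only action stated for a control with a life-threatening TRP; the routine report and the hold on controls leave no written rule that ensures a warning at detection; and the exclusion is a post-randomisation, control-only removal related to the primary outcome. On notification alone this would be close to a missing operational detail. With the one-arm exclusion, a stated rule has a clearly better alternative, so the protocol should be changed.

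Neither the number of patients affected, nor the delay before they are told, nor the size or direction of bias can be given, because the protocol states no frequency of such TRPs and no timing for disclosure. The conclusion assumes that nothing in the unseen consent material or standing local practice imposes the missing duty. It does not assume that pharmacists would stay silent; many would warn the patient anyway, but the protocol leaves that to discretion.

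**What to change.** In the control-group paragraph of section 4, and in the Figure 1 text, replace exclusion with this rule:

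- When a listed life-threatening TRP is found in a control, the hold lifts for that TRP, and the patient and the treating physician are informed promptly. Clinical handling rests with the physician.
- The patient stays in the control group, keeps the 2-3 month visit and is analysed as randomised. The hold continues for the patient's other TRPs.
- For a sudden health episode or complication, which the patient would normally already know of, the rule is physician notice and retention.

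The cost is protocol wording plus one patient contact and one physician alert per affected control. The review, the report and the follow-up visit already exist for controls. The downside is that some controls receive part of the service early, which dilutes the contrast by an amount that the documents do not allow to be quantified: neither the share of controls affected nor the effect in them is given.

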**5. Medication Review:**

The Australian model for medication review service will be followed in this study (since this service does not exist yet in the country). The clinical pharmacist will interview the patients at their own homes; collect all the information relevant to their medications and health conditions including current diseases, current drugs, history of previous diseases and drugs, side effects and allergy. This will be followed by interpretation and analyzing of the information regarding the patient’s medical history, current therapeutic regimen along with any needs and concerns; identifying therapeutic and other issues relevant to the short and long term management of the patient; making appropriate recommendations regarding the clinical information gathered for consideration by a physician.

**6. Pharmacist’s Role in Medication Review**

The pharmacist will provide proper education and counseling for patients regarding their illnesses and medications. In addition, information about the importance of adherence to the therapy will be provided to the patients. Advices regarding self-treatment and herbal remedies abuse will be explained to the patients. Effective, open-ended questioning and active listening will be used in order to achieve proper education for the patients. A patient will learn best by hearing spoken instructions and by directly handling medications.

**7. Baseline Assessments**

At baseline, patients from control and intervention groups will be interviewed at their homes to assess their use of treatment and to collect all relevant information regarding patients' demographics, current diseases, current drugs, history of previous diseases and drugs, side effects and allergy (Appendix 5). In addition, Patients' adherence, anxiety level, quality of life and medication-knowledge level will be assessed (Figure 1).

**8. Follow-up Assessments**

Both groups will be revisited at their homes 2-3 months after the baseline assessment. This assessment traces changes in treatment, number and type of TRPs, adherence, anxiety, quality of life and patients’ knowledge about medication (Figure 1). A collective report highlighting the feasibility and success of the study will be submit to the involved physicians three months following the end of the study.

**9. Adherence to Medication [Appendix 1]**

Questionnaire will be conducted for the patients to assess the patients’ self-reported adherence to their medications. AbuRuz et al. (2011) developed this questionnaire depending on a scale that was developed by Morisky et al. (1986). The questionnaire consists of five items including questions of how often during the last month the patients forgot to take their medication, skipped their medication, stopped their medication when they felt better, stopped their medication when they felt worse or stopped their medication when they experienced side effect. The measurement scale used in this questionnaire is scored at 0 (never), 1 (rarely), 2 (sometimes), 3 (often) and 4 (always). Hence, adherence will be analyzed as a continuous scale out of five (the higher the score is, the less the patient is adherent).

**10. Quality of Life [Appendix 2]**

All patients will be asked to answer the self-completion Quality of Life Questionnaire (EQ-5D questionnaire) which is one of the most commonly used questionnaires to measure health-related quality of life. This questionnaire consists of 5 domains (mobility, self-care, usual activities, pain/discomfort and anxiety/ depression) in which each domain has 5 levels of severity; no problem (level 1), mild problem (level 2), moderate problem (level 3), severe problem (level4) and extreme problem‖ (level5).

**11. Medication knowledge [Appendix 3]**

Patients' knowledge about medication will be assessed by the Knowledge about Drug Therapy Questionnaire that is validated by AbuRuz et al (2011). The questionnaire consists of four questions related to patients' medications including (How, When, Why) is he/she taking the medication, and any other comments they may have related to this medication .

**12. Scale of Anxiety [Appendix 4]**

Patient’s scale of anxiety will be assessed using a questionnaire composed of seven items relevant to generalized anxiety Zigmond & Snaith (1983). The questionnaire is scored at a scale of 4 (0-3).The possible score for each patient will range from 0 t0 21. Hence, the anxiety will be analyzed as a continuous scale out of four (the higher the score is, the more the patient is anxious).

**13. Definition and Classification of TRPs**

AbuRuz *et al*. (2006) classification system will be used in order to identify the TRPs which actually or potentially interfere with the clinical outcomes for each patient. This classification has been widely implemented and carefully explained in prior research (Basheti *et al*.,2013; Basheti *et al*., 2016). In this study, this classification will be used to identify unnecessary drug therapy, untreated conditions, ineffective/incomplete drug therapy, inappropriate dosage regimen, adverse drug effects, actual or potential drug interactions, non-adherence and suboptimal monitoring.

**14. Physicians’ Acceptance of the Clinical Pharmacist Recommendations**

Many physicians will be contacted regarding the TRPs identified for the Syrian patients. This is because different refugees visit different physicians depending on the refugees’ living areas and on the medical organizations that each refuge is visiting. At the end of the study, the total number of the physicians that accept the pharmacist recommendation will be divided by the total number of the contacted physicians to calculate the acceptance rate of the physicians for the pharmacist recommendations.

**15. physicians’ approval rate of the Pharmacist Recommendations**

After the medication review, all the pharmacist’s recommendations will be sent to the physicians to take the approval from them. The physicians will approve some of these recommendations. To calculate the approval rate for the pharmacist recommendation, the total number of approved recommendations by physicians will be divided by the total number of all recommendations (approved + rejected) sent to the physicians.

**16. Sample size**

Sample size determination will be based on the primary outcome variable of TRP improvement pre and post receiving the MMR service. Based on previously published study in this area, and in order to detect a significant different change in TRPs of 1 point difference (Molino *et al*., 2014), with a significance level of 5% and power of 80%, with the standard deviation of the change being 2.92 (variance based on the data from previously published study (Basheti *et al*., 2016)), the minimum required sample size needed will be 138 patients.

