**Study objectives:**

This study sheds light on the following objectives:

1-What is the eventual impact of applying MMR service on decreasing the total number of TRPs identified among study refugees for intervention compared to control group?

2-What is the eventual impact of applying MMR service on the study refugees' Quality of Life (QoL) for intervention compared to control group?

3-What is the eventual impact of applying MMR service on the study refugees' self-reported adherence for intervention compared to control group?

4-What is the eventual impact of MMR service on improving the scale of anxiety for the study refugees for intervention compared to control group?

5-How much will the acceptability rate of the physicians’ acceptance to the MMR service be?

6-What is the physicians' approval rate for the pharmacist’s recommendations regarding the identified TRPs?

7- What are the common types of TRPs identified among the study refugees?

8-What are the frequencies of TRPs identified among the study refugees?

9-What is the intervention group’s perspective of the MMR service?

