**Research Hypothesis**

*Null hypothesis*: The implementation of the MMR service for adult Syrian refugees with chronic conditions in Jordan will have no impact on the number of identified TRPs, anxiety scale, self-reported adherence, patients’ knowledge about their medication and quality of life in comparison to patients that will not receive this service.

*Alternative hypothesis:* The implementation of the MMR service for adult Syrian refugees with chronic conditions in Jordan will have significant impact on the number of identified TRPs, anxiety scale, self-reported adherence, patients’ knowledge about their medication and quality of life in comparison to patients that will not receive this service.

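### Read as a total, 138 patients gives the intervention-versus-control comparison of TRPs about 51% power, not the stated 80%; the between-arm requirement is 135 per arm (270).

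*Protocol*

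**What the plan says.** The first entry under Study objectives asks about the effect of the service on "decreasing the total number of TRPs identified among study refugees for intervention compared to control group". The Research Hypothesis is likewise set against patients who do not receive the service, and Section 3 (Study Design and Clinical Setting) describes randomisation into two groups. The primary question is therefore a between-arm one.

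Section 16 (Sample size) describes its basis differently, as "TRP improvement pre and post receiving the MMR service". Its inputs are:

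- the effect: "in order to detect a significant different change in TRPs of 1 point difference";
- the variability: "with the standard deviation of the change being 2.92";
- 5% significance and 80% power.

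It concludes that "the minimum required sample size needed will be 138 patients". It does not give the test, the sidedness, the allocation ratio, the number per group or an allowance for loss to follow-up.

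**The concern.** A before-after change in one group and a difference in change between two groups need different sample sizes. With the same difference and the same standard deviation, the two-group comparison needs about twice as many patients in each arm as the one-group test needs in all, so about four times as many in total. Section 16 uses before-after wording for a trial whose objective is a randomised comparison, and its total is about half of what that comparison requires.

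The stated power for the primary outcome is at stake. If a true effect of 1 TRP had only about an even chance of reaching significance, a null result would say little about whether the service works. Funders, ethics reviewers and readers would meanwhile have been told that the chance of detecting it was 80%.

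**Working it through.** **Inputs.** All from Section 16: difference 1 TRP, SD of the change 2.92, alpha 5%, power 80%, stated size 138.

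**Assumptions where the protocol is silent.** Two-sided test, because the hypothesis is non-directional ("will have significant impact on the number of identified TRPs"); 1:1 allocation; 138 is the total, so 69 per arm.

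**1. Reproducing 138.** For a one-sample (paired) test of a mean change:

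n = (1.960 + 0.842)² × 2.92² / 1² = 66.9 by the normal approximation.

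The exact t-test calculation gives 79.5% power at n = 68 and 80.1% at n = 69, so n = 69. Doubling for two groups gives 2 × 69 = 138, an exact match.

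**2. Size needed for the between-arm comparison.** For a two-sample comparison of change:

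n per arm = 2 × (1.960 + 0.842)² × 2.92² / 1² = 133.8 by the normal approximation, so 134 per arm (268 in total).

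The t-test needs 135 per arm (270 in total).

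**3. What 69 per arm delivers.** The standard error of the difference is 2.92 × √(2/69) = 0.497.

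| Quantity at 69 per arm | Result |
|---|---|
| Power for 1.0 TRP, two-sided t-test | 51.5% |
| Power for 1.0 TRP, normal approximation | 52.1% |
| Difference detectable with 80% power | 1.40 TRPs (normal approximation 1.39) |
| Half-width of the 95% confidence interval | about 0.98 TRP |

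**4. Other readings that might yield 138 as a total.**

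| Reading | Size needed |
|---|---|
| One-sided 5%, two-sample | 106 to 107 per arm, at least 212 in total (power at 69 per arm is 64%) |
| 1:2 or 2:1 allocation | about 302 in total |
| 2.92 taken as a variance | 46 per arm, 92 in total |

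None gives 138. For 138 in total to provide 80% power between arms, the SD of the change would have to be about 2.1 instead of 2.92.

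**5. Sensitivity to loss (rates assumed; the protocol gives none).** With 10% loss, about 62 per arm remain and power is 47%. With 20% loss, about 55 per arm remain and power is 43%. These figures assume equal loss in both arms. Section 4 also plans to exclude control patients with life-threatening TRPs, which would add loss on one side only and is not modelled here.

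**6. Sensitivity to baseline adjustment (correlations assumed; none is given).** If baseline and follow-up counts have equal variance and correlation r, adjusting follow-up for baseline multiplies the variance of the change-score comparison by (1 + r)/2. At 69 per arm, power for 1.0 TRP becomes 70%, 64% or 58% for r = 0.3, 0.5 or 0.7. Adjustment helps, but does not reach 80% at any of these values.

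**The case against.** The strongest reply is that 138 may mean patients per group. Section 16 says neither total nor per group. A difference in change and an SD of the change are natural inputs to a between-arm comparison of change scores. The two-sample answer of 135 per arm is within 3% of 138, and 138 per arm would give 80.9% power. On that reading the only defect is a missing qualifier.

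This is possible but less likely. A minimum required sample size given as a number of patients, without qualification, reads as the total. No stated allowance lifts 135 to 138, whereas 2 × 69 is exact and fits the before-after wording. In either case the text needs correcting, because recruitment to a total of 138 would stop at about half the required number.

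A second reply is that the doubled paired calculation is an inference. That is correct, since the protocol names no formula, and it should be put as the likely origin. The power shortfall does not depend on it: it follows from the stated difference, SD, significance level and total.

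A third reply is that the analysis model belongs in a statistical analysis plan, and that the figures for baseline adjustment rest on assumed correlations and equal variances. That is fair, and the adjustment is offered below as an option. The finding itself concerns a figure that the protocol states.

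**Conclusion.** The concern holds. As written, Section 16 claims 80% power for a 1-TRP difference, and 138 patients in total provide 51.5% for the randomised comparison, a shortfall of nearly 30 percentage points. The comparison needs 135 per arm (270 in total), or 138 patients can detect 1.40 TRPs with 80% power. This rests on a two-sided test, 1:1 allocation and 138 being the total. A one-sided test raises power only to 64%. If 138 was meant per arm, power is about 81% and the fault is one of wording. Confidence is high in the power figure and somewhat lower in the explanation of how 138 arose.

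**What to change.** First establish whether 138 is the total or the number per arm. Then rewrite Section 16 for the between-arm difference in TRPs, stating the test, sidedness, allocation ratio, number per arm, total and any allowance for loss.

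- **If 138 is per arm:** say so, and give the total of 276.
- **If 138 is the total and the 1-TRP target stands:** plan 135 per arm (270 in total) before any allowance for loss. This costs 132 more patients (270 − 138).
- **If the trial stays at 138 in total:** state about 51% power for 1.0 TRP, or 80% power for 1.4 TRPs. This costs only wording, but the stated power becomes less favourable and the trial remains underpowered for the difference it set out to detect.

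Under any of these, consider defining the primary result as the between-arm difference in follow-up TRP count adjusted for the baseline count. Sections 7 and 8 place interviews at baseline and follow-up in both groups, so no extra data collection is needed. The adjustment would recover part of the lost power, by an amount that depends on a correlation the protocol does not give.
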